#### 2.8.1. Primary Outcome

The primary outcome is resting-state FC. Functional brain alterations in this study will be more sensitive than structural MRI and behavioral performances in detecting the neuromodulatory effect of temporal three-needle therapy.

Resting-state FC analyses can assess synchronous activity between brain regions and be used to study the brain in healthy and disease groups on the brain-network level, which will help to understand (a) markers for diseases, (b) paths to investigate disease mechanisms, and (c) predictors of clinical course [40]. Resting-state FC could serve as a biomarker of motor function recovery in stroke patients with hemiplegia [41]. Stronger FC after stroke correlates with better behavioral outcome [42]. Resting-state FC analysis may offer an invaluable approach to explore functional network reorganization in the brain after stroke. In this study, brain FC plasticity within and beyond the sensorimotor network will be measured by rs-fMRI.

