#### 2.8.2. Secondary Outcomes

The secondary outcomes including ReHo, ALFF, FMA-UL, and MBI will be measured at the same time points of the primary outcome. Brain regional activity (ReHo and ALFF) will be assessed via rs-fMRI. FMA-UL, MBI, and AEs will be assessed by the abovementioned three experience rehabilitative assessors.

ReHo can be used to explore the consistency of neuronal activity in regional brain areas at resting state, which may be a potential biomarker of the neural substrates associated with hand function following stroke [43] and provide an effective tool for evaluating the efficiency of rehabilitative therapies after stroke [44]. An increase in ReHo value indicates that the consistency of neuron activity tends to be increased.

ALFF can reflect the intensity of the nerve activity of a single voxel and hemodynamic BOLD information on neural activity [45]. In addition to FC, regional ALFF may provide complementary information on the neural mechanism [46]. After brain injury, the blood flow of the brain decreases, and the local ALFF value shows a downward trend.

The FMA-UL is used to only assess motor function of the upper limb in stroke patients. Because the motor function of the upper limb is the most difficult to recover after stroke, we focused on upper limb motor dysfunction in this study. The FMA-UL has been shown to be useful for measuring arm and hand motor function, and 30-item assessment shows a longitudinally stable item difficulty order and is valid for measuring volitional arm motor ability over time [47]. The FMA has a total of 100 points for normal motor function. The maximum score for UL is 66. The evaluation includes measuring reflex activity, flexor synergy, extensor synergy, and movement combining synergies, movement out of synergy, elbow, shoulder, wrist, and hand function, and relates coordination and speed. An ordinal scale applied to each item is used: 0 = cannot be performed, 1 = can be partially performed, and 2 = can be completely performed.

The MBI has shown good properties for measuring disability in stroke patients [48] and is the most prevalent functional outcome scale in stroke trials. The MBI covers 10 domains: feeding, grooming, dressing, bathing, toilet transfers, bowel and bladder continence, ambulation, moving between wheel chair bed and back to the wheel chair, and stair climbing. Each item has five levels, with level 5 representing the greatest independence.

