### 2.11. Statistical Analysis

#### 2.11.1. MRI Data Analysis

The DPABI toolkit [49] will be used to analyze the image data on MATLAB2016 (MathWorks) to detect any functional changes (FC, ReHo, and ALFF) in brain neuroplasticity due to temporal three-needle treatment. After data preprocessing, data-driven approach will be conducted to explore neuroplastic changes in the two patient groups and the healthy control group. Data-driven approaches can automatically obtain the brain functional network from the data [50]. Independent component analysis (ICA) based on data-driven approaches is not required to assume a priori that the MRI signal can be separated directly into a series of maximally independent components and associated time courses [51, 52] and different components corresponding to the corresponding resting-state network. FDR correction will be used for multiple comparisons to control the false positivity rate. Pearson's correlation analysis will be utilized to study the relationship between the rs-fMRI metrics and behavioral data.

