#### 2.11.2. Clinical Behavioral Data Analysis

In this study, statistical analyses will be performed by intent-to-treat (ITT) analysis and per-protocol (PP) analysis. The ITT analysis will include not only all patients with valid results but also randomized patients who were discontinued for a period of time for some reason or transferred to another group. For missing values, we will carry over the last observation results to the endpoint so that the number of patients at the endpoint of each group will be the same as that at the beginning of the trial. The PP analysis will be applied to subjects who adhere to the protocol, have good compliance, and complete the process. When differences in the results exist between the two analyses, the final clinical trial results will be discussed and explained. In this study, only those who received more than 70% of the interventions will be considered satisfied compliance. That is to say, in total number of the 10 treatments, subject missing more than 3 treatments will be excluded from the PP analysis due to violation of the protocol.

All differences in the baseline demographic and clinical characteristics between the two patient groups will be analyzed with the chi-squared test or Fisher's exact test for categorical data and with the *t*-test or Wilcoxon rank-sum test for continuous values. Continuous variables will be shown as the means, SDs. Categorical variables will be described as frequencies or percentages. 

All tests will be two-sided, and a *p* value <0.05 will be considered statistically significant. If the difference of the primary endpoint between the experimental group and the control group was statistically significant, the results of the experimental group are superior to that of the control group, and the intervention method could be considered as effective. Therefore, we firstly set the type I error of the primary endpoint at 0.05. If significant, we then go to test the secondary endpoint at 0.05 type I error.

The changes in the FMA and the MBI between pre- and postacupuncture therapy will be analyzed using repeated measures analysis of variance (ANOVA), This analysis will be used to compare differences and to examine the group effect, time effect, and time-group interaction effect.

A post hoc test will be conducted. Within-group differences between pre- and posttreatment will be compared using the paired *t*-test or Wilcoxon signed rank test for continuous data. 

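### The stepwise 0.05 rule does not control error across the four secondary endpoints, and its first step is tied to no single functional connectivity test

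*Protocol article*

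**What the plan says.** Section 2.11.2 sets a two-step rule. For the first step, "we firstly set the type I error of the primary endpoint at 0.05". For the second, "If significant, we then go to test the secondary endpoint at 0.05 type I error". The same section applies one threshold throughout: "All tests will be two-sided, and a *p* value <0.05 will be considered statistically significant". It also reads a significant primary difference as superiority of the experimental group and as grounds to call the intervention effective.

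The endpoints are defined elsewhere:

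- **Primary.** Section 2.8.1 states: "The primary outcome is resting-state FC". On its scope, it says that "brain FC plasticity within and beyond the sensorimotor network will be measured by rs-fMRI".
- **Imaging analysis.** Section 2.11.1 says that a "data-driven approach will be conducted to explore neuroplastic changes in the two patient groups and the healthy control group", using independent component analysis (ICA). On multiplicity it says: "FDR correction will be used for multiple comparisons to control the false positivity rate". It gives neither the FDR level nor the set of tests that forms the family.
- **Secondary.** Section 2.8.2 begins its list with "The secondary outcomes including ReHo, ALFF, FMA-UL, and MBI", which makes four endpoints.

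**The concern.** A stepwise rule protects the error rate only if each step is one defined test, or a set of tests with its own adjustment. Neither step here meets that condition.

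The second step is written for one secondary endpoint, but there are four. No order, split or correction across them is given. The FDR statement sits in the imaging section. It does not reach FMA-UL or MBI, and correction inside a ReHo or ALFF map does not adjust across endpoints.

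The first step refers to the primary endpoint as if it produced one p-value. FC inside and outside the sensorimotor network can produce many, and nothing says which component, pair of networks or map must be significant. Nor is a direction stated, although any significant difference is to be read as superiority.

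At stake are the claim that the therapy is superior, which rests on the first step, and any formal claim on arm function or daily activities, which rests on the second.

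**Working it through.** **Inputs from the protocol article.** Two-sided 0.05 for the primary, 0.05 for the secondary step, and p < 0.05 for all tests (section 2.11.2); four secondary endpoints (section 2.8.2); FDR correction with level and family not given (section 2.11.1).

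**Assumptions.** The number of FC families K, the correlations between endpoints, and an FDR level of 0.05 are not in the document.

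**1. The plan's own figure.** One primary test followed by one secondary test gives 0.05 at each step, as stated. The rule is right for that case.

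**2. Secondary step with four endpoints, first step passed, all four null hypotheses true.**

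- Independent tests: 1 − 0.95^4 = 1 − 0.8145 = 0.185.
- Upper bound under any dependence: 4 × 0.05 = 0.20.
- Equal correlation between four two-sided z-tests, by simulation: about 0.17 at correlation 0.3, 0.16 at 0.5 and 0.11 at 0.8.
- FMA-UL and MBI alone, if independent: 1 − 0.95^2 = 0.0975.

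**3. Secondary step with no effect on any endpoint and a valid first step.** The first step is passed by chance 5% of the time, so, taking the tests as independent, the chance of any false secondary claim is 0.05 × 0.185 = 0.009. The excess in item 2 therefore arises when the FC effect is real, or when the first step is itself inflated.

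**4. First step, no FC effect anywhere.**

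- FDR (Benjamini-Hochberg at 0.05) pooled over all FC tests: simulated chance of any false finding about 0.050.
- FDR run separately in K independent families, any of which may count as success: 1 − 0.95^K, which is 0.0975 for K = 2 and 0.226 for K = 5.

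**5. First step, some FC effects real.** Pooled FDR over 10 independent tests, with very large true effects in 2, 5 or 8 of them, gave at least one false finding with probability 0.115, 0.141 and 0.088. FDR limits the expected share of false findings. It does not limit the chance of any false finding to 5%.

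**6. After correction.** A fixed testing order over the four secondaries gives 0.05. Holm starts at 0.05/4 = 0.0125, so with all four nulls true and independent tests the error is 1 − 0.9875^4 = 0.049. In simulation it was 0.047, 0.043 and 0.032 at correlations 0.3, 0.5 and 0.8. One pre-stated FC contrast gives 0.05 at the first step.

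**The case against.** The strongest objection concerns the primary. A reader might infer that the false-positive rate for FC is several times 5%. The document does not support that. Section 2.11.1 applies FDR to multiple comparisons without limiting it to one map, and the pooled reading holds about 5% when no FC effect exists. The number of components is not stated, so the per-component figures illustrate one possible reading and do not measure this plan's error. Data-driven ICA does not itself inflate a group comparison; harm would come from choosing the component after seeing group results, and the document does not say this will happen. Nor do the two directions of effect inflate a two-sided test. All of this stands.

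It may also be said that the target is partly fixed, since the title and Discussion name sensorimotor network FC and the Discussion gives the contrast as change in experimental versus control. That narrows the field, but the Discussion also includes FC between the sensorimotor and nonmotor networks, so there is still no single test.

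For the secondaries, the singular wording could mean 0.05 for the whole step, with the method left to an analysis plan that is not shown. That each endpoint is tested at 0.05 is indeed an inference, drawn from the singular wording and the threshold for all tests. But a 0.05 limit on the whole step conflicts with that threshold unless some adjustment is added. The article chose to state a confirmatory rule, and the rule as stated does not fit its own list of endpoints.

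Finally, this is small mechanism research. That bears on urgency, but section 2.1 calls the trial a superiority trial and section 2.11.2 attaches a claim of effectiveness to the rule.

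**Conclusion.** The point holds in two parts of different strength.

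**Secondary step: the stated 0.05 is not delivered.** With the first step passed and all four nulls true, the familywise error is 18.5% under independence and about 11% to 17% at the correlations tried. These are conditional figures. They should not be read as the trial's overall false-positive rate, which for the secondaries is about 1% when nothing is affected and the first step is valid. The condition still matters, because a real FC effect is the situation in which the secondaries are meant to be tested.

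**Primary step: 0.05 is not assured.** The superiority rule is tied to no named contrast and no FDR family. The error is about 5% with pooled FDR and no FC effect, and higher if FDR is run per component. When some FC effects are real, FDR is not familywise control. No single inflated figure can be given.

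**What to change.** **(a) Primary.** Name one sensorimotor-network FC contrast, the between-group difference in change from baseline, as the only test that opens the second step, at two-sided 0.05. Claim superiority only in a pre-stated direction. Report all other FC components and network pairs as exploratory, with FDR and a stated family. The ICA can stay if the sensorimotor component and its summary value are chosen without regard to group.

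The choice must be fixed before any A-versus-B comparison of imaging data. Fixing it before unblinding is not enough: under section 2.6 the statisticians work with groups labelled A and B, and the code is disclosed only after the analysis, so a choice made after seeing group differences would still meet that condition.

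**(b) Secondary.** Replace the single secondary test with a pre-stated fixed sequence over the four endpoints, stopping at the first non-significant result, or with Holm across them. ReHo and ALFF each need one pre-set summary value to enter either procedure.

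**Cost.** No new data or patients are needed; the change is to the text and to the timing of one decision. The price is that some secondary endpoints may not be formally tested and that the remaining FC maps become exploratory.

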## 2. Methods

### 2.1. Study Design and Setting

This study will be a two-week, prospective, randomized, patient-assessor blind, controlled, single-center, superiority, neuroimaging trial with two-parallel patient groups and a healthy control group. This study will take place mainly in Shenzhen Nanshan District People's Hospital, Shenzhen, Guangdong Province, China. In this trial, we will recruit subjects into two categories. The first category will comprise healthy controls, and the second will comprise patient subjects. A total of 20 age-, gender-, and education-matched healthy subjects will be recruited into the healthy control group. The purpose of healthy control recruitment is to establish a baseline normal MRI data set to facilitate comparison with the MRI data of the patients' groups. The healthy control group will receive baseline MRI scans without any intervention. Forty eligible patients will be randomized into two groups: (1) the experimental group and (2) the control group, with a 1 : 1 allocation ratio. All patients will take medicine for secondary prevention of stroke (e.g., antihypertensive, hypoglycemic, antiplatelet, and hypolipidemic drugs) and conventional rehabilitative treatments according to the Chinese stroke rehabilitation treatment guidelines [5] (e.g., physical therapy (PT) and occupational therapy (OT)); these treatments will be consistent across the patient groups. In the control group, patients will receive acupuncture at MS6 following basic drug treatments and conventional rehabilitative treatments. Patients in the experimental group will receive temporal three-needle acupuncture 5 days per week, 10 sessions over 2 consecutive weeks, plus basic drug treatments and conventional rehabilitative treatments. Acupuncturists with at least 10 years of clinical experience will perform acupuncture therapy (including temporal three-needle therapy and MS6 therapy). Professional rehabilitative therapists with above 5 years of clinical experience will conduct conventional rehabilitative treatments (PT and OT) for the patients.

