### 2.2. Sample Size Calculation

Our primary outcome will be resting-state FC measured by rs-fMRI. Because millions of voxels are used to indirectly estimate the blood oxygen level-dependent (BOLD) signal and traditional power calculations are of no significance [32], we calculated the sample size according to the relevant published articles. Previous rs-fMRI study of the acupuncture mechanisms in stroke had a sample size of 20 cases for the healthy control group [33]. Moreover, a study on the effects of sample size on cerebral response to acupuncture with fMRI had shown that the imaging results in 17 healthy controls were similar to the results of studies with 21 cases [34], which may suggest that approximately 20 subjects maybe a relatively common choice in rs-fMRI studies after acupuncture. The sample size in acupuncture mechanism study using rs-fMRI with stroke patients typically ranges from a few cases to approximately 20 cases [33, 35–37]. Because this trial is a neuroimaging study, the primary outcome will be based on the subjects' MRI image processing, and patients with left cerebral ischemia accompanied by right limb hemiplegia will be enrolled in this study so as to ensure the relative consistency of cerebral ischemia lesions and reveal the neuroimaging mechanism more regularly.

Under the condition of left brain ischemia stroke with right limb hemiplegia in this study, we plan to enroll 20 patients diagnosed with ischemia stroke in each patient group (20 in the experimental group and 20 in the control group) and 20 healthy volunteers in the healthy control group.

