AEs will be tabulated and summarized using descriptive statistics. The AEs incidence of each group will be confirmed as evaluation index, and the computation formula is as follows: AEs incidence% = (number of AEs/total number of cases in this group) × 100%. The current version of STATA 12.0 statistics (StataCorp, Texas, USA) will be used for statistical analyses.

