### 2.13. Investigation of Adverse Events and Safety

Intervention-related AEs might include edema due to bleeding, bending and breaking of the needle, fainting during acupuncture, and retained needle after treatment. During the course of the study, any AEs including the onset of clinical symptoms, degree of symptom severity, persistence time, treatment, and sequelae will be recorded. AEs will be compared between patients in the experimental group and the control group and will be recorded in the CRF and assessed by the research staff at each visit. Serious AEs will be reported to the ethics committee immediately.

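### The adverse-event index divides events by patients but is labelled an incidence percentage, so it can exceed 100% and misrank the arms if events recur

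*Protocol article*

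**What the plan says.** The AE paragraph that closes section 2.11.2 of the protocol article does three things. It states that "AEs will be tabulated and summarized using descriptive statistics". It gives one figure a special role: "The AEs incidence of each group will be confirmed as evaluation index". It then gives the formula for that figure: "AEs incidence% = (number of AEs/total number of cases in this group) × 100"%.

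Section 2.13 covers collection and use. Any AE during the study is recorded, and AEs "will be recorded in the CRF and assessed by the research staff at each visit". The same section announces a between-arm comparison: "AEs will be compared between patients in the experimental group and the control group". It names no method for it.

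The exposure is set elsewhere. Section 2.1 gives the experimental group "10 sessions over 2 consecutive weeks", and Table 2 (item 6b) gives the control group the same needling details and regimen. Section 2.2 plans "20 in the experimental group and 20 in the control group". No section says that a patient with several AEs enters the index once.

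**The concern.** An incidence percentage is a proportion of patients, so numerator and denominator must both count patients. Here the numerator counts events. The two agree only if no patient has more than one AE, and the design leaves room for repeats: ten needling sessions per patient, with AEs assessed at each visit. The only AE-related removal rule, in section 2.4.3, concerns serious events, so it does not cap repeated minor ones.

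The index is the one AE figure that the article defines for each group, so it is the natural figure for the comparison announced in section 2.13. A reader who sees a percentage will take it as the share of patients affected. If AEs recur, that reading is too high. Because recurrence can differ between arms, the order of the arms can also be wrong.

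**Working it through.** The article gives no AE count or rate, so there is no stated figure to reproduce. The check evaluates the stated formula at the planned design and compares it with the proportion of patients affected. All event counts and per-session probabilities below are assumptions.

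**Inputs from the article**
- Patients per arm: n = 20 (section 2.2), allocated "with a 1 : 1 allocation ratio" (section 2.1).
- Sessions per patient: s = 10 (section 2.1; Table 2 for the control group), so up to 20 × 10 = 200 sessions per arm.

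**The two measures**
- Stated index = 100 × (number of AEs) / n.
- Patient-level incidence = 100 × (patients with at least one AE) / n.

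**Upper limit.** The patient-level figure cannot exceed 100%. The stated index passes 100% at 21 events: 21/20 = 105%. One AE at each session would give 200/20 = 1000%. That is a theoretical bound, not a forecast.

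**One patient with repeated events (assumed counts)**

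| AEs in one patient | Stated index | Patients affected |
|---|---|---|
| 1 | 1/20 = 5% | 1/20 = 5% |
| 3 | 3/20 = 15% | 5% |
| 8 | 8/20 = 40% | 5% |
| 10 | 10/20 = 50% | 5% |

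**Order of the arms (assumed counts).** In arm A one patient has 10 AEs: index 50%, patients affected 5%. In arm B four patients have one AE each: index 4/20 = 20%, patients affected 20%. The index ranks arm B as safer, although four times as many of its patients had an AE.

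**Range over AE frequency.** Assume at most one AE per session, with probability p, independent across sessions. The expected index is 100 × 10p. The expected patient-level incidence is 100 × [1 − (1 − p)^10].

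| p per session | Stated index | Patients affected | Gap (percentage points) | Chance that an arm exceeds 100% |
|---|---|---|---|---|
| 1% | 10% | 9.6% | 0.4 | practically 0 |
| 5% | 50% | 40.1% | 9.9 | about 0.001 |
| 10% | 100% | 65.1% | 34.9 | about 0.44 |

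The last column is the probability of more than 20 events in 200 sessions, from a binomial distribution. If AEs cluster in some patients, the index keeps the same expected value while fewer patients are affected, so the gap widens.

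**If the percentages were tested as proportions.** Take one patient with 10 AEs in one arm and one patient with one AE in the other. Entering these as 10/20 v 1/20 gives a Fisher's exact p of 0.003. The patient-level comparison is 1/20 v 1/20, with p = 1.00. The article does not plan such a test; the example shows only what the label could lead to.

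**The case against.** Four objections deserve an answer.

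1. **It may be a slip of wording.** The label and the patient denominator both suggest that the numerator was meant to be patients with AEs. That is plausible, but nothing in the article confirms it, and the correction is the same either way.

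2. **Events per patient is a legitimate summary.** It is, under its own name. The fault lies in calling it an incidence percentage.

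3. **Repeats may be uncommon.** Section 2.4.2 excludes people with needle phobia or fainting with needles, and section 2.4.3 removes participants with serious AEs. Both narrow the scope for repeats without capping minor events. If AEs are rare, the 1% row shows that the error hardly matters. This part of the objection stands and limits the size of the point.

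4. **Little in the trial depends on the index.** AEs are among the outcome measurements in section 2.8, but section 2.8.2 does not list them with the secondary outcomes when it opens. Neither the sample size nor the ordered testing of endpoints uses the index. This stands too.

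A reader might go further and infer that the planned AE comparison is statistically invalid because repeated events in one patient are not independent. The article does not support that. It describes the AE summary as descriptive and names no AE test; the chi-squared and Fisher's tests in section 2.11.2 are for baseline characteristics. Non-independence would matter only if the percentages were tested as proportions.

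**Conclusion.** The formula is wrong as written for the quantity it names. It yields events per patient times 100, which is not an incidence proportion, has no ceiling at 100%, and can put the arms in the wrong order. This follows from the stated rule and does not depend on any detail left to a fuller document.

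The size depends on how often AEs recur, on which the article is silent. Under the independence assumption, the overstatement runs from 0.4 percentage points at 1% per session to 34.9 at 10%. The single-patient and reversed-order examples show what is possible, not what is expected. The point concerns the definition and labelling of a descriptive safety index. It does not touch the primary outcome.

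**What to change.** Replace the formula in section 2.11.2 with: AE incidence (%) = patients with at least one AE / all treated patients in the group × 100. State that each patient is counted once. State also that treated patients who discontinue stay in the denominator and, if affected, in the numerator; this is needed because section 2.4.3 excludes participants with serious AEs from the study, and the present denominator does not say whether they still count.

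Report the number of events, or events per session delivered, on a separate line under its own label. Confidence intervals or a Fisher's exact comparison of the patient-level proportions are optional; the defect is cured without them.

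The cost is one formula and one or two sentences. Each AE is already recorded in the case report form, so patients with at least one AE can be counted from data that the trial collects anyway. Section 2.14 places the trial in its recruitment phase, so on the article's account the change can be made before analysis.
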